## Summary

Identifying and effectively reducing FD in community-dwelling older Australians is of significant interest to policy makers and clinicians. To date, there is no valid or reliable way of identifying FD in any setting, and FD identification usually occurs at crisis health presentations to hospital, rather than in community health settings under ‘usual’ circumstances. Thus, many individuals go undetected, until their capacity to live independently and safely in the community is in question. Our research is the first that we know of, to propose that a real risk of downstream FD in an older person can be identified within four weeks of an ED presentation for a minor health event, using low mental quality of life scores. We further propose that early community-based interventions for people identified as having risks of FD can prevent or delay its onset.

## Methods

### Study design

TRIIFL is a randomized controlled trial (RCT) nested in a 13-month longitudinal cohort study (Figure 1).

**Figure 1 F1:**
[figure not shown]
Study design – RCT nested in a longitudinal cohort study.

#### Study 1: Longitudinal cohort study

The total sample is recruited in Study 1. Every participant will be assessed for FD outcomes and predictors over the following 13 months (at five time points) using a battery of tests.

### Setting, timing

Eligible individuals will be recruited from the ED of a large metropolitan hospital in Adelaide, South Australia, between April and June 2014, using the recruitment process successfully piloted in our 2011 study [37].

### Eligibility criteria

Inclusions

● 65 years old or older

● Presented to ED with non-catastrophic health conditions which do not result in admission to hospital for further care

Exclusions

● Suffering communicable diseases requiring isolation

● Current mental health crisis

● Under detention

● Diagnosis of dementia

● Unable to communicate in English

● Profoundly deaf (such as would limit telephone communication at follow-up)

To remain eligible for the study, individuals must not subsequently become an inpatient as a result of the index ED presentation (that is, must be discharged directly to home from ED). Subsequent hospital admissions and/or ED presentations (unrelated to the index ED presentation) do not compromise eligibility, as this information, captured at each follow-up, is important to build a service-usage profile. Being a ‘frequent flyer’ to ED does not compromise eligibility, as these individuals may well be on the cusp of FD and are not detected, despite multiple ED presentations.

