### Baseline screening

We will collect data in the ED (baseline) on consenting, eligible participants from

•the electronic hospital admissions system - age, gender, residential details, differential diagnosis; and

•a test battery as successfully piloted in our 2011 study [37]. This captures the highest level of schooling, primary language, ED presentations and hospitalizations in the past six months, falls in the past twelve months using the Falls Risk in Older People - Community (FROP_COM) instrument [39], living arrangements, requiring a carer, receiving community services, type and use of gait aid, iADLs[19] and cognition with the Mini Mental State Examination (MMSE) [40].

Based on data from our pilot study, we will additionally apply the Katz *et al*. [18] 20 basic ADL instrument and two quality of life measures – the SF12 [41,42] and the Australian Quality of Life (AQoL 4D) [43]. By collecting both basic and iADL scores, we can provide comprehensive ADL information about the target population to compare with international data. The SF12 provides the opportunity for international population-based comparisons of quality of life [41,42] with our sample of older ED presenters. The AQoL, which has not previously been used for older people discharged from ED, provides an Australian perspective on health-related multi-attribute utility quality of life [43], and allows production of health cost effectiveness data (quality-adjusted life years (QALYs)), and estimation of burden of disease.

This total test battery takes an average of 5.5 minutes to administer. All but two questions are delivered verbally by the recruiting researcher, who records the answers. The older person only has to write responses to two MMSE questions.

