### Study 1 analysis

FD will be assessed as change from baseline at each time point as:

•One or more falls increase from the baseline rate

•More than one event of hospitalization, or ED presentation, from the baseline rate

•Decrease of one point in any item of the ADL instrument [18], or

•Decrease of 2+ points from baseline total iADL score [19], or any decrease in baseline score in the domains of home activities, doing laundry, shopping and getting places (we previously reported these domains as critical to functional independence) [37]

•Scores decreasing from above median at baseline in either physical or mental domain, to below median in the SF12 [41,42]

•Any decrease in AQoL_4D (in the manner recently described for chronic obstructive pulmonary disease (COPD))[44]

•Change to a more assistive gait aid (for example, a one point stick to a four-pronged stick)

•Change in living arrangements to more supported care

•Increased carer involvement

•Greater type and frequency of use of formal community services or informal supports

•More frequent GP attendances.

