### Study 2: nested RCT

#### Subject selection and randomization

All participants in Study 1 will be stratified at one-month telephone follow-up into low and high scores on the MCS domain of the SF-12, (SF12-MCS), using the median cut point. We previously reported this as a transformed score of 55 [37], which is comparable to the same age-gender population SF-12 norms [41]. The nested RCT will be conducted involving only the subjects with lower than median SF12-MCS scores at this time point (Figure 1).

An independent trials office will randomize these subjects using a computer generated random number series, into an individualized person-centered community-based intervention, or ‘usual care’ which reflects no intervention. It is unlikely that any intervention would normally be offered to this population as it is not current practice to screen people for low mental component quality of life scores after an ED contact.

Considering Studies 1 and 2, there are three study cohorts (Figure 1):

•Subjects with SF12-MCS scores ≥55, who will be observed only, for 13 months after recruitment (12 months after the one month SF12 scores are taken) (the observed cohort)

•Subjects with SF12-MCS scores <55, from which two RCT groups will be allocated one month after recruitment, randomized into

•Intervention specifically tailored to address the individual’s problems, concerns, and goals (low SF12-MCS, intervention cohort)

•No treatment (low SF12-MCS, no treatment cohort).

Outcome measures for the two RCT groups will be taken at three-, six- and twelve-month time points after randomization (four, seven and thirteen months post-recruitment).

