The three study cohorts will be assessed at time of allocation into a study arm (one-month after recruitment) for homogeneity in key socio-demographic characteristics and immutable factors (for example, gender, age, schooling, postcode, diagnosis) and all outcome measures (including the percentage of ‘frequent flyers’ in each arm). We previously reported this as one or more ED contacts per month over the preceding 12 months [33,34].

Change over time in each outcome measure will be calculated using repeated measures analysis of variance (ANOVA) models, with study contact point, cohort (1, 2, or 3) and key demographic features as independent variables. Partial Least Squares (PLS) models using pathway analysis will be applied to the multiple outcome, immutable and mutable independent variables at each time point, to determine different spatial arrangements and the significant factors which impact on data clusters.

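### A fixed rise of more than one hospital or ED event counts as functional decline whatever the prior use, so stable frequent attenders are flagged by chance several times as often as stable low users, which can bias the non-randomised cohort comparison

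*Protocol article*

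**What the plan says.** All places are in the protocol article.

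- **Eligibility criteria** admits frequent attenders on purpose: "Being a ‘frequent flyer’ to ED does not compromise eligibility, as these individuals may well be on the cusp of FD".
- **Analysis of data from Studies 1 and 2** says what such a person is: "We previously reported this as one or more ED contacts per month over the preceding 12 months".
- **Baseline screening** records "ED presentations and hospitalizations in the past six months".
- **Table 1** (Outcome measures) gives look-back windows for hospitalizations of 1, 3, 3 and 6 months at the 1-, 4-, 7- and 13-month contacts.
- **Study 1 analysis** opens the FD definition with "FD will be assessed as change from baseline at each time point as" and gives the service-use criterion as "More than one event of hospitalization, or ED presentation, from the baseline rate". Nothing ties the increment to the person's own level of use.
- **Analysis of data from Studies 1 and 2** also compares the cohorts at allocation on "all outcome measures (including the percentage of ‘frequent flyers’ in each arm" and plans the main model: "Change over time in each outcome measure will be calculated using repeated measures analysis of variance (ANOVA) models".
- **Subject selection and randomization** covers only the two low SF12-MCS groups: "An independent trials office will randomize these subjects using a computer generated random number series". The high SF12-MCS cohort is observed and not randomised.

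**The concern.** A rise of two events is unusual for someone who seldom attends hospital and ordinary for someone who attends monthly. With one threshold for both, the criterion partly measures how much a person used services before, and not whether use has increased.

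Study aim 2a asks whether a low SF12-MCS score at one month identifies incipient FD. Hypotheses 1 to 3 set the FD experience of the three cohorts side by side. Hypothesis 1 expects no FD on any measure in the observed cohort, and Hypothesis 2 is met by FD on any one measure, so a false flag on this single criterion counts. If low scorers attend the ED more often but at a steady rate, they will collect more service-use FD than high scorers and the screen will look better than it is. If the high scorers attend more, the error runs the other way.

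The problem is separate from the unequal look-back windows. It remains when baseline and follow-up are put on the same time base, as is done in the check.

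**Working it through.** The plan states no misclassification rate for this criterion, so there is no figure to reproduce.

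**Inputs from the documents.** Baseline window 6 months; post-randomisation windows w = 3, 3 and 6 months; flag when the rise exceeds one event; frequent attender at r = 1 contact per month or more.

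**Assumptions.** Each person has a constant rate r per month (no true change). Counts are Poisson and independent between windows. The hospitalization windows in Table 1 also apply to ED presentations. The baseline count is scaled to the follow-up window. The lower comparison rates (0.1, 0.25 and 0.5 per month) are illustrative.

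**Rule.** B ~ Poisson(6r), Y ~ Poisson(w·r); flag if Y − B·w/6 > 1.

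**Per contact.** At 13 months both windows are 6 months, so the chance of a flag is the exact tail P(Y − B ≥ 2) of a difference of two Poisson counts with mean 6r. At r = 0.1 (mean 0.6) it is 7.5%; at r = 1 (mean 6) it is 33.0%. At the 4- and 7-month contacts, summing over B gives 3.3% and 26.7%. The false-flag rate thus differs by a factor of 33.0/7.5 = 4.4 at 13 months and 26.7/3.3 = 8.1 at the earlier contacts.

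**At least one flag over the three post-randomisation contacts** (simulation; the contacts share one baseline count):

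| Stable rate per month | 4 mo | 7 mo | 13 mo | At least once |
|---|---|---|---|---|
| 0.1 | 3.3% | 3.3% | 7.5% | 13.4% |
| 0.25 | 11% | 11% | 18% | 34% |
| 0.5 | 19% | 19% | 27% | 46% |
| 1.0 | 27% | 27% | 33% | 56% |

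**Sensitivity at r = 1.**

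- *Observed rather than true frequent attenders.* Among people with a true rate of 1 per month, those actually seen 12 or more times in the prior year are flagged 18%, 18% and 20% per contact, 41% at least once.
- *Raw counts, no scaling.* 6%, 6% and 33%; 36% at least once.
- *Increment read as more than one event per month.* 7%, 7% and 3%; 15% at least once over three contacts, 27% when the 1-month contact is included.
- *Index visit counted in the baseline.* 45% at least once.
- *Overdispersed counts (gamma shape 2 per window).* 33%, 33% and 39%; 64% at least once.

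The level moves with the reading, but the rise with prior use remains. With raw counts, for example, the ever-flagged share is 11% at 0.1 per month against 36% at 1 per month.

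**Effect on a cohort comparison.** Suppose a share p of a cohort is at 1 per month and the rest at 0.1, all stable. The ever-flagged share is 55.8p + 13.4(1 − p) percent.

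- p = 10% v 3%: 17.6% v 14.7%, a gap of 0.07 × 42.4 = 3.0 points.
- p = 20% v 5%: 21.9% v 15.5%, a gap of 0.15 × 42.4 = 6.4 points.

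At the 13-month contact alone the gaps are 0.07 × 25.5 = 1.8 and 0.15 × 25.5 = 3.8 points.

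**The case against.** The strongest reply is that the main model does not use this flag. The repeated measures ANOVA is run on each outcome measure, the RCT is sized on iADL and SF-12 scores, and the share of frequent attenders is compared between cohorts at allocation, so an imbalance would be seen. This stands in part: an ANOVA on the event counts does not inherit the defect. But the aims and hypotheses are worded in terms of FD, and the list under Study 1 analysis is the only working definition of it. A check at allocation reveals an imbalance without correcting for it. The model names only contact point, cohort and key demographic features, and states no adjustment for prior use.

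Three stronger readings are tempting, and the documents do not support them.

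- *Stable frequent attenders are classed as declining about half the time.* FD is judged at each contact, where the figure is 27–33% at one contact per month. About half describes only being flagged at least once, which the protocol nowhere defines as the outcome, and it falls to 41% among those observed with 12 or more contacts in the prior year.
- *The trial comparison is biased.* The two low SF12-MCS arms are randomised, so prior use is balanced in expectation. There the rule adds chance events, not expected bias.
- *Low scorers are known to use the ED more.* Nothing in the document gives prior use by SF12-MCS group, so neither the direction nor the size of any gap is established.

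It is also fair to say that this is one of eleven FD criteria and that a gap of 3 to 6 points is modest.

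**Conclusion.** The concern holds for the service-use criterion and for the non-randomised comparison of low with high SF12-MCS cohorts. With no change in anyone, a fixed increment flags a person at one contact per month about 4 to 8 times as often per contact as a person at 0.1 per month. A cohort with higher prior use can therefore show more FD without any decline. The per-person rates rest on constant Poisson rates and a scaled baseline. The cohort gap of about 3 to 6 points rests further on assumed shares of frequent attenders and could be smaller, larger or reversed. This is worth correcting before analysis because it bears on aim 2a, but it does not threaten the randomised comparison beyond added noise.

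**What to change.** For cohort and arm comparisons of hospital and ED use, do not rely on the fixed-increment flag. Compare the change in event rate: a count model with a person-time offset and allowance for overdispersion, reporting the follow-up-to-baseline rate ratio by cohort. Stable use then gives a ratio of about 1 at any level of prior use. State how the 1-, 3- and 6-month windows are put on one time base. State also that the index visit, which everyone has by design, is left out of the baseline count. Keep the criterion in Study 1 analysis as descriptive, and report it by level of prior use.

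The cost is slightly more analysis work and a group-level rather than per-person result for this criterion. No new data are needed.

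A per-person threshold that widens with the expected count is possible but is a trade-off, not a correction. With a two-standard-deviation condition that includes the sampling error of the baseline count, ever-flagged false positives at one contact per month fall from 56% to about 15%. Detection of a true doubling in a 6-month window falls from about 86% to about 45%. That is a heavy price where the purpose is to detect early decline.

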### Baseline screening

We will collect data in the ED (baseline) on consenting, eligible participants from

•the electronic hospital admissions system - age, gender, residential details, differential diagnosis; and

•a test battery as successfully piloted in our 2011 study [37]. This captures the highest level of schooling, primary language, ED presentations and hospitalizations in the past six months, falls in the past twelve months using the Falls Risk in Older People - Community (FROP_COM) instrument [39], living arrangements, requiring a carer, receiving community services, type and use of gait aid, iADLs[19] and cognition with the Mini Mental State Examination (MMSE) [40].

Based on data from our pilot study, we will additionally apply the Katz *et al*. [18] 20 basic ADL instrument and two quality of life measures – the SF12 [41,42] and the Australian Quality of Life (AQoL 4D) [43]. By collecting both basic and iADL scores, we can provide comprehensive ADL information about the target population to compare with international data. The SF12 provides the opportunity for international population-based comparisons of quality of life [41,42] with our sample of older ED presenters. The AQoL, which has not previously been used for older people discharged from ED, provides an Australian perspective on health-related multi-attribute utility quality of life [43], and allows production of health cost effectiveness data (quality-adjusted life years (QALYs)), and estimation of burden of disease.

This total test battery takes an average of 5.5 minutes to administer. All but two questions are delivered verbally by the recruiting researcher, who records the answers. The older person only has to write responses to two MMSE questions.

### Outcome measures

At one, four, seven and thirteen months after recruitment, all participants will be contacted by telephone and consent sought for interview. Socio-demographic information will be confirmed, and all outcome instruments and mutable independent variables will be recorded (Table 1). Semi-structured questions will be asked about how participants are managing, their concerns and reasons for subsequent hospitalizations and ED presentations. At the four, seven and thirteen month data collection points (after nested RCT commencement), assessors will be blinded to group allocation.

**Table 1 T1:** Timeframes of outcome measurements

**Measures**	**Baseline**	**1 month**	**4 months**	**7 months**	**13 months**
ADLs	√	√	√	√	√
iADLs	√	√	√	√	√
SF12	√	√	√	√	√
AQoL_4D	√	√	√	√	√
Falls	√ (last 12 months)	√ (last month)	√ (last 3 months)	√ (last 3 months)	√ (last 6 months)
Hospitalizations	√ (last 6 months)	√ (last month)	√ (last 3 months)	√ (last 3 months)	√ (last 6 months)
Gait aid (type)	√	√	√	√	√
Living arrangements	√	√	√	√	√
Carer engagement	√	√	√	√	√
Organized (formal) community services	√	√	√	√	√
GP visits	√	√	√	√	√
Informal community supports	√	√	√	√	√
Satisfaction with community supports	√	√	√	√	√

ADLs, activities of daily living; AQoL_4D, Australian Quality of Life; GP, general practitioner; iADLs, instrumental activities of daily living; SF12, Short Form-12 Health Survey; √ indicates an occasion of data collection.

### Additional data and calculations

From baseline information on age, iADLs and MMSE scores, a HARP score will be determined [17,36]. HARP, while sensitive to approximately 63% only, is useful for comparing FD risk in our sample with other Australian and international studies. Validation details of the index ED presentation will be undertaken via patient record audit to verify age, presenting diagnosis, previous hospitalizations and ED discharge plans (if any).

### Study 1 analysis

FD will be assessed as change from baseline at each time point as:

•One or more falls increase from the baseline rate

•More than one event of hospitalization, or ED presentation, from the baseline rate

•Decrease of one point in any item of the ADL instrument [18], or

•Decrease of 2+ points from baseline total iADL score [19], or any decrease in baseline score in the domains of home activities, doing laundry, shopping and getting places (we previously reported these domains as critical to functional independence) [37]

•Scores decreasing from above median at baseline in either physical or mental domain, to below median in the SF12 [41,42]

•Any decrease in AQoL_4D (in the manner recently described for chronic obstructive pulmonary disease (COPD))[44]

•Change to a more assistive gait aid (for example, a one point stick to a four-pronged stick)

•Change in living arrangements to more supported care

•Increased carer involvement

•Greater type and frequency of use of formal community services or informal supports

•More frequent GP attendances.

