### Hypotheses

As shown in Figure 2, our hypothese are:

1. The observed cohort will not demonstrate FD over the following 12 months in any FD measure.

2. The low SF12-MCS, no treatment cohort will demonstrate significant FD in any one or more outcome measures, taken over the next three months, when compared to their baseline recruitment status.

3. The low SF12-MCS, intervention cohort will show no FD (comparable findings to the observed cohort) over the next 12 months.

4. Additionally, those individuals in the low SF12-MCS, no treatment cohort who demonstrate significant FD at three months follow-up, and who access ‘rescue’ intervention (see Section on Ethics), will show an attenuated rate of FD over the following twelve months, compared with the rate they exhibited in the first three months.

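### Falls and hospital events are flagged as functional decline against a baseline rate with no time unit and a different look-back, so the false-flag probability changes from contact to contact

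*Protocol article*

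**What the plan says.** The Study 1 analysis section opens its list of criteria with "FD will be assessed as change from baseline at each time point as". Two of the criteria are event counts: "One or more falls increase from the baseline rate" and "More than one event of hospitalization, or ED presentation, from the baseline rate". Both state the increment as a number of events, and neither gives the baseline rate a time unit.

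The look-backs are fixed elsewhere. Baseline screening records "ED presentations and hospitalizations in the past six months, falls in the past twelve months". Table 1 (Outcome measures) confirms "last 12 months" for baseline falls and 6 months for baseline hospitalisations. For both items it sets follow-up recall at 1 month (1-month contact), 3 months (4- and 7-month contacts) and 6 months (13-month contact). ED presentations have no row in Table 1. The text says they are asked about at follow-up but gives no window.

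Under Hypotheses, the untreated low-score cohort "will demonstrate significant FD in any one or more outcome measures, taken over the next three months, when compared to their baseline recruitment status", so one criterion is enough.

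**The concern.** A count increment is interpretable only if the two counts cover the same length of time. Here they almost never do. Falls windows never match, hospitalisation windows match only at 13 months, and ED follow-up windows are not stated.

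Calling the reference a rate does not settle the matter. An analyst could compare raw counts, shrink the baseline count to the follow-up window, or scale the follow-up count up to the baseline window. Each reading gives a different flag rate.

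FD over time is the subject of the trial. Hypothesis 1 expects none in the observed cohort on any measure. Hypothesis 2 compares the 3-month status of the untreated cohort with recruitment. Hypothesis 4 compares an early rate of decline with a later one. If the false-flag rate moves with the window, part of the reported course of FD comes from the recall schedule.

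**Working it through.** The plan gives no figure for these rules, so there is none to reproduce; the 50 per arm rests on iADL. The check asks how often a person whose true risk does not change is flagged.

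**Inputs from the document.** Baseline look-back b is 12 months for falls and 6 for hospitalisations. Follow-up look-back f is 1, 3, 3 and 6 months. The increment k is 1 for falls. For hospital events, more than one is read as k = 2.

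**Assumption.** The document gives no event rates. I take a constant Poisson rate r per year, from 0.3 to 4 for falls, with baseline and follow-up counts independent: X ~ Poisson(r·b/12), Y ~ Poisson(r·f/12).

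**Three readings of the rule.**
- Raw counts: Y ≥ X + k
- Baseline prorated to the follow-up window: Y ≥ X·f/b + k
- Follow-up scaled to the baseline window (annualised, for falls): Y·b/f ≥ X + k

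**Worked case: falls, r = 1, 3-month window (mean 0.25).**
- Raw: Σ P(X = x)·P(Y ≥ x + 1) = 0.3679 × 0.2212 + 0.3679 × 0.0265 + 0.1839 × 0.0022 + … = 0.0915, or 9.2%.
- Annualised, 4Y ≥ X + 1: P(Y = 1)·P(X ≤ 3) + P(Y ≥ 2) = 0.1947 × 0.9810 + 0.0265 = 0.2175, or 21.8%.

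**Falls: % flagged at unchanged risk, 1- / 3- / 6-month windows**

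| Falls per year | Raw counts | Baseline prorated | Annualised |
|---|---|---|---|
| 0.3 | 1.8 / 5.4 / 10.5 | 1.8 / 5.4 / 10.6 | 2.5 / 7.2 / 13.5 |
| 0.5 | 2.5 / 7.3 / 14.2 | 2.5 / 7.4 / 14.4 | 4.1 / 11.7 / 20.4 |
| 1 | 3.1 / 9.2 / 18.1 | 3.1 / 9.8 / 19.6 | 8.0 / 21.8 / 31.2 |
| 2 | 2.4 / 8.2 / 18.3 | 3.2 / 12.7 / 25.1 | 15.4 / 35.0 / 38.6 |
| 4 | 0.9 / 4.7 / 14.8 | 4.9 / 20.1 / 31.5 | 28.3 / 41.4 / 42.2 |

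With gamma-mixed rates (shape 1, mean 1 a year) the pattern holds: 2.1 / 6.6 / 13.6 raw and 7.7 / 17.9 / 23.9 annualised.

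**Size against a real change.** On raw counts, a true doubling of risk from 1 to 2 falls a year, seen through a 3-month window, flags 18.1%. That equals unchanged risk at 1 a year seen through the 6-month window, because both follow-up means are 0.5 (2 × 3/12 = 1 × 6/12).

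**Hospitalisations, 1 a year, 1- / 3- / 6-month windows**

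| Increment | Raw counts | Scaled to 6 months |
|---|---|---|
| k = 2 | 0.2 / 1.7 / 5.9 | 8.0 / 14.4 / 5.9 |
| k = 1 | 4.9 / 14.2 / 26.7 | 8.0 / 20.4 / 26.7 |

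The readings agree only at the 6-month window, where baseline and follow-up match. With k = 2, going from the 3- to the 6-month window raises the flag rate on raw counts and lowers it when scaled.

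**The case against.** Several points on the other side are sound.

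- **Risk still matters.** A reader might infer that the flag follows window length instead of risk. It follows both: at 1 fall a year, doubling the true risk raises the 3-month raw-count flag from 9.2% to 18.1%.
- **One pair is matched.** Hospitalisation at 13 months is 6 v 6 months, so the mismatch does not cover every contact.
- **The doubling between 7 and 13 months depends on the reading.** It appears on raw counts (9.2% to 18.1% at 1 fall a year) and roughly with a prorated baseline. Annualised, the step is 21.8% to 31.2% at 1 a year and 41.4% to 42.2% at 4 a year. The 1-month window stays well below the others even then (28.3%).
- **Equal windows are no cure for false flags.** With 12 v 12 months at 1 fall a year, 34.6% are flagged at unchanged risk. Most false flags come from an any-increase rule on a sparse count; the windows explain why the level differs between contacts.
- **The randomised comparison.** It is tempting to say that the trial result is biased. Both arms share the same windows, so their contrast at a given contact is not biased by this alone. The analysis section for Studies 1 and 2 does not say that the binary flag is the between-arm endpoint, so a loss of information there is not shown either.

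It may also be said that a time unit is a detail that a condensed article leaves to the full protocol. That does not answer the point. The article itself fixes the thresholds, the contacts and the look-backs, and as fixed they do not fit together.

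**Conclusion.** The concern holds in a limited form. The falls and hospital/ED criteria compare event counts over unequal periods, against a rate with no unit. At unchanged risk the falls flag varied with the window under every reading and every rate tried. At 1 fall a year, from the 1- to the 6-month window, it rises about six-fold on raw counts and about four-fold annualised (31.2/8.0). For hospitalisations even the direction depends on the reading. Two analysts following the same text could report quite different FD.

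The damage is to FD classification within cohorts and to its course across contacts, chiefly hypotheses 1, 2 and 4. For hypothesis 2, which rests on one contact, it concerns the level of FD and not a trend.

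The percentages rest on assumed Poisson rates, with one overdispersed check. The effect on the full FD classification, which has eleven criteria, was not computed. The plan should be changed, but this does not threaten the validity of the randomisation-based comparison.

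**What to change.** Do not classify falls or hospital events as FD by a count increment over a baseline of different length.

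- **Across contacts and cohorts:** analyse falls and hospitalisations as event rates per person-month, with log look-back time as an offset.
- **RCT:** compare total counts between the arms over the 12 months after randomisation. The 3 + 3 + 6-month windows are contiguous and cover that year. Negative binomial regression with the baseline count as covariate would serve.
- **If a binary item is kept:** define it only on matched look-backs, for example hospitalisation 6 v 6 months at the 13-month contact, and state the increment and time unit.
- **ED presentations:** record them over the same follow-up windows as hospitalisations and add them to Table 1.

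For falls and hospitalisations the data are already scheduled, so the cost is analysis work. ED presentations need a stated recall window at follow-up. The price is that these items leave, or change within, the per-contact FD definition, so the hypotheses that rely on it need matching wording.
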